## Abstract

**Background:**

Fibromyalgia is a disease with an increasing incidence. It impairs the quality of life of patients and decreases their functional capacity. Aquatic therapy has already been used for managing the symptoms of this syndrome. However, aquatic therapy has only recently been introduced as a treatment modality for improving proprioception in fibromyalgia. The main objective of this study is to determine the effectiveness of two physiotherapy protocols, one in and one out of water, for improving balance and decreasing pain in women with fibromyalgia.

**Methods/Design:**

The study protocol will be a single-blind randomised controlled trial. Forty women diagnosed with fibromyalgia will be randomly assigned into 2 groups: Aquatic Therapy (*n* = 20) or Land-based Therapy (*n* = 20). Both interventions include 60-min therapy sessions, structured into 4 sections: Warm-up, Proprioceptive Exercises, Stretching and Relaxation. These sessions will be carried out 3 times a week for 3 months. Primary outcomes are balance (static and dynamic) and pain (intensity and threshold). Secondary outcomes include functional balance, quality of life, quality of sleep, fatigue, self-confidence in balance and physical ability. Outcome measures will be evaluated at baseline, at the end of the 3-month intervention period, and 6-weeks post-treatment. Statistical analysis will be carried out using the SPSS 21.0 program for Windows and a significance level of *p* ≤ 0.05 will be used for all tests.

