#### Pressure Pain threshold (PPT)

This is defined as the minimum pressure that triggers a painful response. An electronic algometer (Commander™ Algometer de JTECH Medical) will be used to measure the PPT on the 18 tender points, according to the ACR criteria [1]. The unit of pressure measurement will be kg/cm2, and the assessments will be done bilaterally, always beginning from the point located on the right. To avoid the risk of temporal summation [29], each tender point will be assessed only once. A 1 cm^2^ rubber tip will be used to centralise the pressure, the 18 tender points are:Occiput: Suboccipital muscle insertion.Supraspinatus muscle: Supraspinatus tendon, above medial scapular spine.Trapezius: Midpoint of the upper border.Greater trochanter: Posterior to the greater trochanter of the femur.Gluteus maximus: Upper outer quadrant of the buttocks in the anterior muscle fold.Lower cervical: Anterior C5-C7 intertransverse space.Second intercostal space: At the second costochondral junction.Lateral epicondyle: 2 cm distal to the lateral epicondyle.Medial knee: Medial fat pad of the knee, proximal to the joint line.

The procedure will be explained to the patients and demonstrated by performing a measurement on a non-included point. The rubber tip of the algometer will be placed perpendicularly to the skin and patients will have to say “stop” when the pressure begins to be painful.

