### Statistical issues

#### Sample size calculation

The sample size was calculated to find a difference of ± 2.5 points between intervention groups on the VAS pain intensity scale [40], with a standard deviation of 2.5 points [41].

In order to achieve a statistical power of 80% with a significance level of *p* ≤ 0.05 and assuming a 20% dropout rate, an estimated 20 participants are required in each of the intervention groups. This sample size allows for detecting differences of 2 ± 2 s in the TUG test, with a statistical power of 80% and a significance level of *p* ≤ 0.05, assuming a 20% dropout rate.

The sample size was defined for a bilateral hypothesis and was carried out by the ENE software.

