### Statistical analysis

Analysis will be descriptive of all outcomes included in the study, expressing quantitative outcomes with their mean ± standard deviation and qualitative outcomes with their absolute value, percentage and 95% confidence intervals.

The association between qualitative outcomes will be studied using the Chi-square test. After checking normality with the Kolmogorov-Smirnov test, the Student *T* test or the Mann–Whitney *U* test will be used to perform mean comparison. The mean comparison between two or more categories will be studied with the ANOVA test or Kruskal-Wallis test, as appropriate.

The correlation between quantitative outcomes will be analysed with the Pearson or Spearman correlation coefficients, as appropriate.

The mean comparisons for related outcomes in two different moments will be studied with the Wilcoxon test. Friedman test will be used when comparing more than two moments. In addition, the clinical relevance of the intervention will be studied by calculating the relative risk, relative risk reduction, absolute risk reduction and the number needed to treat. All of these measures will be presented with their 95% confidence interval.

A multivariate analysis by multiple linear regression or logistic regression to adjust for the effectiveness of the intervention according to possible confounding factors and to determine what other outcomes might be associated with each result will be carried out. Only the outcomes that show a statistical significance p <0.20 in the bivariate analysis, will be included in the multivariate regression analysis. In addition, a stepwise backward modelling strategy will be carried out.

All analysis will be done by intention to treat [42], where the total value of randomisation is preserved and control of any counfounders’ effect is insured.

The significance level set for all the analysis will be *p* ≤0.05. The SPSS statistical software, version 21.0 (SPSS, Chicago, IL) will be used for all analysis.

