## Discussion

The main objective of this randomised controlled trial is to determine the effectiveness of two physiotherapy protocols in improving balance and decreasing pain in women with FM, at the end of the intervention and at 6-weeks follow-up. With the study conclusion, we expect to test the following null hypothesis: “There is no difference in balance or pain for participants undergoing physiotherapy interventions on land or in water”. The balance disorder observed in FM is a sympton that has been discovered only recently. This is why there are very few publications regarding. Specifically, in the MEDLINE database, we were able to identify only 11 randomized controlled trials that included physical interventions and balance improvement was included in their objectives. Of these 11 clinical trials, only three included physiotherapy as a treatment method [43–45]. Given this, we expect the study conclusion to contribute to the fund of scientific knowledge, providing evidence that physiotherapy is a safe and effective tool in the management of FM symptoms, specifically balance disorders and pain.

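### Four unranked primary outcomes, no primary variable or visit, and 0.05 for every test: the stated 5% is not the error rate of a claim that water and land differ in balance or pain

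*Protocol article*

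**What the plan says.** The abstract states "Primary outcomes are balance (static and dynamic) and pain (intensity and threshold"). The Primary outcomes section defines these as follows:

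- **Static balance:** Romberg's test in four conditions, filmed and reduced by the CvMob software to four parameters, on medio-lateral and anterior-posterior axes.
- **Dynamic balance:** TUG time, and a gait test giving speed, step length and step height.
- **Pain intensity:** one visual analogue scale (VAS).
- **Pressure pain threshold (PPT):** an algometer "will be used to measure the PPT on the 18 tender points", with no summary score given.

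Measurements are taken at baseline, at the end of treatment and six weeks later. The Discussion sets the objective "at the end of the intervention and at 6-weeks follow-up", without making either visit primary, and poses a single null hypothesis covering balance or pain.

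On the error level, the abstract gives p ≤ 0.05 and says it "will be used for all tests". The Statistical analysis section repeats it: "The significance level set for all the analysis will be" p ≤ 0.05. No order, composite or correction is stated.

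On size, "The sample size was calculated to find a difference of ± 2.5 points between intervention groups on the VAS pain intensity scale", with a remark that the same number also serves TUG. Neither is called the lead outcome.

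**The concern.** A 5% level protects a conclusion only if one pre-specified test, or a controlled set of tests, decides it. Here the conclusion spans four constructs and two visits, and each result is judged at 0.05. The Interventions section says the two programmes were made alike so that a significant difference could be attributed to the environment. With nothing ranked, such a claim could rest on one sway parameter, one tender point or one visit. The protocol would not show whether that result had been the intended one. The reader could not tell a confirmatory finding from a chance one, and selective emphasis would be hard to detect.

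**Working it through.** **1. The plan's own sample size.** Inputs from the Sample size calculation section: difference 2.5, SD 2.5 (standardised effect 1.0), power 80%, p ≤ 0.05, 20% dropout; "The sample size was defined for a bilateral hypothesis".

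n per arm = 2 × (1.960 + 0.842)² × (2.5/2.5)² = 15.7, rounded up to 16. Then 16 / (1 − 0.20) = 20 per arm, as stated. TUG (2 s, SD 2 s) has the same standardised effect and gives the same 16 and 20. So the figure is right for one comparison at the full 0.05 and makes no allowance for a second.

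**2. How many primary variables per visit.**

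- Romberg: 4 conditions × 2 axes × 4 parameters = 32
- Gait: 3
- TUG: 1
- VAS pain: 1
- PPT: 18

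Total 32 + 3 + 1 + 1 + 18 = 55. Narrower readings:

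- Total speed counted once per condition: Romberg is 4 × (1 + 3 × 2) = 28, total 51.
- X mean dropped, because Table 1 defines it only as position in the video frame: 32 − 8 = 24, total 47.
- PPT averaged to one value: 55 − 17 = 38.
- X mean dropped and PPT averaged: 24 + 3 + 1 + 1 + 1 = 30.

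**3. Chance of at least one false positive when there is no effect.** For k independent tests at 0.05 it is 1 − 0.95^k. For k = 4 this is 1 − 0.8145 = 18.5%. For correlated tests I took standard normal test statistics with one common pairwise correlation r. The documents give no correlations, so r is an assumption.

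| Tests counted | r = 0 | r = 0.5 | r = 0.7 |
|---|---|---|---|
| 4 (one per construct, one visit) | 18.5% | 16% | 13% |
| 8 (one per construct, two visits) | 34% | 25% | 19% |
| 30 (narrow count, one visit) | 79% | 51% | 34% |
| 55 (full count, one visit) | 94% | 64% | 42% |

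**4. What control would cost in power.** Two-sample t-test, standardised effect 1.0, 16 completers per arm:

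- alpha 0.05: 78%. This is slightly below 80% because step 1 uses the normal approximation.
- alpha 0.025 (two outcomes): 68%
- alpha 0.0125 (four outcomes): 57%

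In a fixed sequence of two outcomes at 0.05, with both effects real, the first keeps 78%. The second needs both tests to succeed: 0.781 × 0.781 = 61% if independent, 64% at an assumed r = 0.3 and 66% at r = 0.5.

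**The case against.** The strongest reply is that a count of 55 is not a count of planned tests. The article says the CvMob parameters will be studied. It does not say that every stance, axis, parameter and tender point gets its own between-group comparison. A PPT summary and a choice among sway parameters are details an article may leave to a fuller document. This stands, and it is why the count is given as a range and the four-test case is shown beside it.

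A reader might also infer that about 110 tests are planned (55 at each of two visits), or that a false positive is more likely than not. The documents support neither. The Statistical analysis section names Wilcoxon and Friedman tests for change over time, and does not state a between-group test of each variable at each visit, so 110 is a ceiling. Whether the one-visit chance exceeds one half depends on the assumed correlation: at r = 0.7 it is 34% for 30 variables and 42% for 55. Nor does the article say that a single significant component rejects the joint null; it gives no decision rule.

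It may be said that the sample size points to VAS pain as the lead outcome. It suggests this but does not designate it, and the Background says that balance is the protocol's focus.

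The unseen analysis plan does not remove the point. The 0.05 rule is stated twice for all tests, so a later correction would have to contradict this text.

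**Conclusion.** The point holds. Four constructs are primary, no variable or visit is singled out, and each test is run at 0.05. On the narrowest reading, four tests at one visit, the chance of a false claim is 13% to 18.5%, about 2.6 to 3.7 times the stated 5%. Using both visits raises it to 19% to 34%. If the individual variables are each tested, it is 34% to 79% for 30 and 42% to 94% for 55 at one visit. These figures assume no true effect, a common pairwise correlation between 0.7 and 0, and that any one significant result would be presented as a difference in balance or pain. The safe conclusion is an error rate well above 5%, of uncertain size. The 20 per arm is correct for a single comparison; the fault lies in how many comparisons share the 0.05.

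**What to change.** Before anyone sees outcomes by group, amend the text to:

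1. Name one primary post-baseline visit, for example the end of the 3-month treatment.
2. Limit confirmatory between-group tests to the two outcomes the sample size covers: VAS pain intensity and TUG time.
3. Hold the overall two-sided level at 0.05 in one of two ways. One is a fixed sequence, with the order chosen and justified by the sponsor in view of the stated focus on balance. The other is a split of alpha, 0.025 each or by Holm's method.
4. Reduce PPT to one value per patient, for example the mean of the 18 points.
5. Label the Romberg/CvMob, gait, PPT and other-visit results as secondary or exploratory, and confine the 0.05 statement to the confirmatory set.

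Cost: a dated amendment to the protocol and analysis plan, with the registered primary outcomes checked for consistency (the registry record is not among the documents). No patients or measurements are added. With a fixed sequence, the second outcome cannot be confirmatory if the first fails; with pain first, no balance result could then be confirmed. With a 0.025 split, power per outcome falls from 78% to 68% under the planned effect with 16 completers per arm. A lone sway, gait or PPT result could no longer be called primary, so static balance and pain threshold lose that status. The sponsor should make that choice openly.

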**Discussion:**

This study protocol details two physiotherapy interventions in women with fibromyalgia to improve balance and decrease pain: aquatic therapy and land-based therapy. In current literature there is a lack of methodological rigour and a limited number of studies that describe physiotherapy protocols to manage fibromyalgia symptoms. High-quality scientific works are required to highlight physiotherapy as one of the most recommended treatment options for this syndrome.

**Trial registration:**

Date of publication in ClinicalTrials.gov: 18/02/2016. ClinicalTrials.gov Identifier: NCT02695875.

## Background

Fibromyalgia (FM) is a chronic disorder characterized by widespread pain in combination with tenderness in at least 11 of 18 established tender points [1]. In 2010, following the release of the new diagnostic criteria of the American College of Rheumatology (ACR) [2], a new definition for FM was adopted. In addition to pain, it includes other important symptoms such as fatigue, restless sleep, cognitive problems and a variety of somatic symptoms.

The mean prevalence rate of FM in Europe is 2.5% [3], and the prevalence in Spain in those greater than 20 years of age is 2.4% [4]. Worldwide, the incidence of FM is increasing at an exponential rate, demonstrating that FM is a common clinical condition that will require increasing specialised attention. FM causes disability, which is associated with high indirect costs derived from absenteeism and the use of health care resources. This is not only a major health problem, but also a significant socioeconomic problem [4]. There are many available treatments to manage FM, however, only a few are supported by scientific evidence. The latest report of the European League Against Rheumatism (EULAR) [5] agrees with current clinical practice guidelines (CPG) which state that aerobic exercise is the only treatment option for the management of FM based on strong scientific evidence. CPG from Germany and Israel consider aquatic therapy as the best aerobic exercise program for this type of patient [6] however, for the EULAR, the effectiveness of exercise does not depend on the environment where it is performed (in or out of water).

Both land-based and aquatic therapy programs have shown benefit in the treatment of FM. Land-based treatment includes different types of exercises that train aerobic ability, strength or flexibility [7] in a specific or general manner. Improvements in pain intensity, physical function and quality of life have been noticed. However, there are few studies with an appropriate methodological design that describe the intervention protocol and include physiotherapy as a treatment method. The properties of water make the aquatic environment one of the best places to carry out an exercise program: It reduces the impact on joints, improves microcirculation, facilitates relaxation, decreases the number of contractures and improves muscle tone due to its natural resistance [8]. Nevertheless, despite aquatic therapy showing benefits for the management of some FM symptoms, results should be analysed with caution because of the low methodological quality of studies [9].

Pain and quality of life are the most studied outcomes in FM. This protocol will focus on balance. Recently, it has been shown that patients with FM have problems with motor control [10] and postural balance [11]. Numerous observational studies have shown that there is a real balance disorder in patients with FM [12–14]. The results revealed patients’ difficulty to move quickly or to change center of body mass, while maintaining postural stability. Patients also perceive their own impaired balance, with 45% self identifying this problem as one of the ten most debilitating symptoms of FM [15]. Lack of self-confidence in balance seems to have a direct relationship with muscular strengh and an inverse relationship with pain, disease severity and frequency of falls [16].

Nowadays, health professionals agree that non-pharmacological therapy should be the first choice of treatment for FM, leaving the pharmacological therapy as a second-line intervention [5]. This fact reveals the importance of researching and developing new and effective forms of treatment that constitute reliable and safe alternatives for patients with FM.

The main objective of this study is to determine the effectiveness of two physiotherapy protocols for improving balance and decreasing pain in women with FM.

## Methods

### Study design

The study will be a single-blind randomised controlled trial.

### Enrollment and eligibility criteria

The sample will consist of 40 women, members of the “Fibromyalgia, Chronic Fatigue Syndrome and Multiple Chemical Sensitiviy Association” (ACOFIFA), in A Coruña (Spain).

### Inclusion criteria

Female.Age range between 35 and 64 years [17].FM diagnosis according to the ACR criteria: 1990 [1] and 2010 [2].Mark ≥ 4 on “Visual Analogue Scale” (VAS) for pain.Mark ≥ 5 on EVA for balance, included in the “Revised Fibromyalgia Impact Questionnaire” (FIQR).

### Exclusion criteria

Medical history of severe trauma.Neurological diseases.Frequent migraines.Diabetes.Severe psychiatric diseases.Peripheral nerve entrapment.Inflammatory rheumatic diseases.Pregnancy.People who suffered traumatic injuries in the past 6 months.Chlorine allergy.Anxiety conditions related to water.Infectious diseases.Severe cardiovascular disease.Heat intolerance.Patients who do exercise regularly.Significant changes in pharmacological treatment during the study period.

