### Procedures

The assessments will take place at the Faculty of Physiotherapy of the University of A Coruña (Spain). Three assessment blocks will be established to carry out the measurements. A group of blinded trained assessors will be in charge of each block. In the first block, sociodemographic data (years since FM diagnosis, marital status, employment status, education level, smoking, number of falls in the last 6 months and medication) and anthropometric data (age, weight, height and body-mass index) will be registered. Pain intensity, fatigue, sleep quality, quality of life and self-confidence in balance will also be assessed. The second block will focus on measuring the pain threshold for the 18 tender points and functional independence in performing activities of daily life. Finally, the third block will assess physical ability and static/dynamic balance. Patients will be evaluated at three different moments: At baseline, immediately after the end of treatment and at 6-weeks follow-up.

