### Randomisation

Once the patients have read and signed the informed consent, those who have met the inclusion criteria, will be randomly assigned to one of the two intervention groups:Active Control Group: Land-based exercise program (CG *n* = 20).Experimental Group: Water exercise program (EG *n* = 20).

The randomisation will be carried out in a 1:1 manner via a computer-based scheme. The allocation will be concealed using sealed and opaque envelopes, numbered consecutively [18]. An independent researcher who will not participate in other study procedures will perform the randomisation process. The flow diagram of the study is summarised in Fig. 1.

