### Interventions

The interventions designed in this protocol consist of two similar physiotherapy protocols for people with FM. Both will include 60-min sessions that will be carried out 3 times a week for 3 months by a physiotherapist, in groups of 8–9 people maximum.

Both interventions will be based on: 15 min of warm-up, 25 min of proprioceptive exercises, 8 min of stretching and 12 min of relaxation.

For adequate training of balance and postural control, patients will be required to contract their local musculature (“core stability”) before starting any specific exercise. The transversus abdominis, pelvic floor muscles, internal oblique and multifidus form the local musculature. The most important aspect of achieving core stability will be co-activation of the first two muscles, for which patients will have to place their pelvis in a neutral position. Before starting the interventions, patients will receive anatomy and palpation classes to aid in identification of the involved musculature and how its contraction is perceived.

The protocols have been created by the main researcher based on available scientific evidence. The protocols were designed with the intention of being as similar as possible in order to attribute any statistically significant difference in outcomes between the two groups to the environment where the interventions were performed. Sessions will be pre-programmed with a progression in difficulty over the intervention period: Shorter pauses, higher exercise intensity, eyes closed, etc.

Patients will not be allowed to begin any other activity during the study period. They will have to report any problems, whether event-related or not, as well as any medication changes.

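### An exclusion criterion that can only be met after randomisation is not reconciled with the intention-to-treat rule

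*Protocol article*

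**What the plan says.** Four parts of the protocol article bear on this.

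- **Exclusion criteria.** The last item is "Significant changes in pharmacological treatment during the study period". The article does not define which changes count as significant.
- **Randomisation.** After consent, "those who have met the inclusion criteria, will be randomly assigned to one of the two intervention groups". Eligibility is therefore settled before allocation.
- **Interventions and Procedures.** Treatment lasts 3 months. During the study, participants have a reporting duty: "They will have to report any problems, whether event-related or not, as well as any medication changes". No consequence is attached to a report. Assessments are timed as follows: "At baseline, immediately after the end of treatment and at 6-weeks follow-up".
- **Statistical analysis.** "All analysis will be done by intention to treat [42], where the total value of randomisation is preserved".

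No section says whether a woman whose medication changes stops the programme, leaves follow-up or is left out of the analysis. No section says expressly that she stays in.

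**The concern.** The other exclusion items describe a woman's history or state and can be checked at screening. This one depends on what happens between allocation and the last assessment, roughly four and a half months later. As an exclusion applied at that point, it would take randomised women out of the trial, whereas intention to treat keeps them in.

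This matters because the trigger may be tied to outcome. Pain is a primary outcome, and a woman whose pain is not relieved may change her medication. If such removals differ between the pool and land groups, the women left are no longer the groups that randomisation formed. With 20 per arm, a handful of removals can shift the estimate. Because the threshold is undefined, someone also has to judge each case after allocation. The assessors are blinded, but the article does not say who makes this judgement or whether that person is blinded.

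**Working it through.** **1. Timing.** Eligibility is checked, then women are allocated, then treated for 3 months, then followed for 6 weeks. A change during the study is learned from reports made along the way. For a randomised woman, the criterion can only be triggered after allocation.

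**2. The plan's own sample size.** Inputs from Sample size calculation: difference 2.5 VAS points, SD 2.5, two-sided 5%, power 80%, dropout 20%.

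- n = 2 × (1.960 + 0.842)² × (2.5/2.5)² = 15.7, so 16 per arm
- 16 / (1 − 0.20) = 20 per arm

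The stated 20 per arm is reproduced, as is the TUG statement (2 s, SD 2 s, the same ratio of 1). The sample size is not in question here.

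**3. Room for removals.** The dropout allowance is 20 − 16 = 4 women per arm. The article does not say whether removals for medication change count within it. Power with n analysed per arm is Φ(√(n/2) × 2.5/2.5 − 1.96):

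| Analysed per arm | Power |
|---|---|
| 20 | 88.5% |
| 16 | 80.7% |
| 15 | 78.2% |
| 14 | 75.4% |

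**4. Possible bias.** The article gives no rate of medication change and no link between change and pain, so both are assumptions. Simulation: no true difference, normally distributed pain with SD 2.5, 20 per arm. In each arm, a fixed share of women is removed by a score that has the stated correlation with pain, and a t-test is run on the rest. The removed share of 20 women is 1 (5%), 2 (10%), 4 (20%) or 6 (30%).

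| Removed, arm A v arm B | Correlation 0.3 | Correlation 0.5 | Extreme: exactly those with most pain |
|---|---|---|---|
| 20% v 10% | 0.11 points | 0.19 points; error 6.3% | 0.38 points; error 12% |
| 20% v 5% | 0.17 points | 0.30 points; error 7.3% | 0.58 points; error 15% |
| 30% v 10% | 0.21 points | 0.37 points; error 7.8% | 0.73 points; error 21% |

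At correlation 0.3, type I error is 5.2% to 5.8% across the three rows. If removal is unrelated to pain, there is no bias, only lost precision.

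**5. What drives the extreme column.** With equal removal in both arms the bias is zero by symmetry. Even so, removing exactly those with most pain gives a type I error of about 8% at 10% v 10% and about 10% at 20% v 20%. Cutting off one tail shrinks the observed SD, and the t-test then overstates precision. Much of the 12% at 20% v 10% is therefore this artefact and not a difference between arms.

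**6. Scale.** Against the 2.5-point design difference, 0.11 to 0.37 points is 4% to 15% (0.11/2.5 and 0.37/2.5). The extreme 0.73 points is 29%.

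**The case against.** The strongest reply is that the article does not say these women are deleted from the analysis. The item stands in an eligibility list, and the only statement about the analysis set is the intention-to-treat sentence, which covers all analyses. The duty to report medication changes carries no removal. Two readings would be compatible with that sentence: a loosely worded screening condition (no significant change planned or expected), or an end to participation in the programme while the data stay in the analysis.

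This stands in part. A reader might infer that the two rules can never both be followed, but the text does not go that far: the conflict arises if the criterion is applied as a removal. The screening reading is weakened by the reference to the study period, and neither reading is written down.

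A reader might also infer that medication change is a result of the allocated treatment and that removal must flatter the less effective arm. The article supports neither. Medication may change for unrelated reasons. A woman who improves may reduce her medication and be removed from the better arm, which reverses the sign of the bias.

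Finally, the removal rates are assumed, and 30% in one arm (6 women) exceeds the allowance of 4. The extreme column is therefore a bound and not an expectation.

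**Conclusion.** The point holds as an unreconciled conflict. The exclusion list contains an event that can be observed only after randomisation. If it is applied by removing women, it contradicts the intention-to-treat rule and can bias the comparison in a direction that cannot be known in advance. This is not a detail that an article merely leaves to a fuller document, because both statements are made here and pull apart.

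Under the assumptions shown, the plausible size is modest: about 0.1 to 0.4 VAS points and 5% to 8% type I error. The 0.4 to 0.7 points and 12% to 21% apply only if exactly the women with most pain are removed. Because removal from the analysis is inferred and not stated, and the plausible bias is small beside the design difference, this is something the sponsor should fix, without evidence that the planned comparison is invalid.

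**What to change.** Reconcile the Exclusion criteria and Statistical analysis sections:

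- Limit the medication item to what can be checked before randomisation.
- State that every randomised woman stays in follow-up and in the primary analysis, in her allocated group, whatever happens to her medication.
- Tabulate by arm the medication changes that participants already have to report under Interventions.
- If an analysis without women who changed medication is wanted, label it a sensitivity analysis and define a significant change beforehand.

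The cost is one reworded line in the eligibility list and a sentence or two in the analysis section; no new data are needed. The downside is that the estimate then includes the effect of any change in co-medication. How medication is handled clinically is for the sponsor to decide.
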